## Abstract

**Background:**

Multiple Sclerosis (MS) is an incurable, chronic, potentially progressive and unpredictable disease of the central nervous system. The disease produces a range of unpleasant and debilitating symptoms, which can have a profound impact including disrupting activities of daily living, employment, income, relationships, social and leisure activities, and life goals. Adjusting to the illness is therefore particularly challenging. This trial tests the effectiveness of a Cognitive Behavioural intervention compared to Supportive Listening to assist adjustment in the early stages of MS.

**Methods/Design:**

This is a two arm randomized multi-centre parallel group controlled trial. 122 consenting participants who meet eligibility criteria will be randomly allocated to receive either Cognitive Behavioral Therapy or Supportive Listening. Eight one hour sessions of therapy (delivered over a period of 10 weeks) will be delivered by general nurses trained in both treatments. Self-report questionnaire data will be collected at baseline (0 weeks), mid-therapy (week 5 of therapy), post-therapy (15 weeks) and at six months (26 weeks) and twelve months (52 weeks) follow-up. Primary outcomes are distress and MS-related social and role impairment at twelve month follow-up. Analysis will also consider predictors and mechanisms of change during therapy. In-depth interviews to examine participants' experiences of the interventions will be conducted with a purposively sampled sub-set of the trial participants. An economic analysis will also take place.

**Discussion:**

This trial is distinctive in its aims in that it aids adjustment to MS in a broad sense. It is not a treatment specifically for depression. Use of nurses as therapists makes the interventions potentially viable in terms of being rolled out in the NHS. The trial benefits from incorporating patient input in the development and evaluation stages. The trial will provide important information about the efficacy, cost-effectiveness and acceptability of the interventions as well as mechanisms of psychosocial adjustment.

**Trial registration:**

Current Controlled Trials ISRCTN91377356

## Background

### Psychological adjustment to Multiple Sclerosis

Multiple Sclerosis (MS) is an incurable, chronic and unpredictable disease of the central nervous system. The disease is characterized by the destruction of the myelin sheath surrounding the nerves resulting in the formation of plaques. These plaques disrupt the transmission of nerve impulses leading to the symptoms of the illness which include, but are not limited to, spasticity, loss of balance and co-ordination, blurred or double vision, blindness, numbness, speech distortions, bladder and bowel problems, fatigue, pain and cognitive dysfunction [1]. Plaques can occur in a variety of sites resulting in substantial variation in the type and nature of the symptoms across individuals. The course of the illness is also highly variable and unpredictable [1]. The majority have either a relapsing-remitting or a relapsing-progressive course. Patients experience periods of partial or total remission where the illness is inactive, interspersed with symptom relapses. MS can also have a chronic-progressive course, in which there is a progressive worsening of symptoms and disability. Patients may be initially diagnosed with one type of MS, but over time progress to another.

MS is thought to affect more than 2.5 million people worldwide and around 400,000 people in the United States and 85,000 people in the United Kingdom currently live with the disease [2,3]. The illness is more common in females than males. The cause of the illness is largely unknown and there is currently no cure. Treatment focuses on the management of the patient's symptoms and reducing the number and severity of relapses.

Individuals who have MS are faced with uncertainty about the future, unpleasant and unpredictable symptoms, treatment regimes and drug side effects. MS can have profound consequences including disruptions to life goals, employment, income, relationships, social and leisure activities and activities of daily living. Therefore it is not surprising that it poses multiple challenges for psychological adjustment. A large body of empirical literature attests to poor adjustment outcomes in MS including elevated rates of depressive symptomology or distress [4-7], increased anxiety [5,8], poor subjective well-being and quality of life [5,9], and social role and relationship difficulties [4,10]. On the other hand, research and clinical experience suggests that a substantial proportion of people with MS manage to adapt well to living with the illness [11,12].

Illness factors such as the extent of neurological disability, symptom severity, remission status and length of illness can influence levels of adjustment or a sense of well-being and quality of life [13,14]. However, psychological factors can be as important in predicting and explaining individual differences in adjustment [14,15]. A systematic review conducted as pilot work for this trial demonstrated that a range of psychological factors were associated with adjustment outcomes in MS [16]. For instance, people reporting high levels of perceived social support showed better adjustment [17,18], as did individuals with high levels of optimism and hope [19,20] and those who engaged in health behaviours such as exercise [21]. Use of problem-focussed coping strategies such as planning was also consistently associated with more positive outcomes. On the other hand, emotion-focussed coping strategies including wishful thinking and escape/avoidance were consistently linked with worse adjustment [22,23]. High perceived levels of stress were also linked to worse adjustment [23]. Similarly, a tendency to interpret events, the illness and MS symptoms in an overly negative fashion has been linked to worse adjustment [24-26]. Since many of these factors are potentially modifiable through psychological intervention there is reason to conclude that a programme of therapy that addresses a number of these factors may lead to improvements in adjustment.

In the intervention literature to date targets of psychological interventions for people with MS, particularly Cognitive Behavioral Therapy (CBT), have been mostly centred on the alleviation of depression [27-29]. Two systematic reviews of psychological interventions for MS suggest that there is some evidence that cognitive behavioural approaches can be beneficial in the treatment of depression, and in helping people to adjust to, and cope with having MS[15,30] However, both reviews also criticise the methodological quality of the intervention studies to date. Many have small sample sizes and many inadequately report details of their intervention and trial methodology. This makes it hard to draw definitive conclusions about the efficacy of CBT in this area. Both reviews conclude that further, well-designed trials of CBT-based approaches are warranted. One in particular, concludes that existing research on adjustment and coping looks encouraging and that approaches that target the time period soon after diagnosis and see adjustment as an ongoing process would be useful [15]. This review also draws particular attention to the importance of following the CONSORT statement [31] for reporting such trials and using manuals to make replication of interventions possible.

### Background to the project

Given the evidence that CBT is helpful in improving mental health and psychological aspects of chronic health conditions, we wanted to investigate the efficacy of CBT in helping people with MS adjust to the psychological and social challenges of living with the disease. Although there are some differences between regional MS services in the United Kingdom in availability of information, advice and support in the early stages of MS, formal psychological interventions are not routinely available.

The aim of this project is to assess whether CBT can enhance the adjustment of people in the relatively early years of dealing with MS. Unlike most previous studies which have evaluated the use of CBT in this group [15,30], the focus of this study is to improve broadly defined adjustment outcomes rather than restricting the scope of the intervention to reducing psychiatric morbidity in MS populations where individuals meet criteria for psychiatric disorder. By focusing the intervention on the earlier years of MS it is hoped that patients will learn strategies that will assist in managing the illness in the future.

Because most MS patients receive little structured psychological support, CBT will be compared to Supportive Listening therapy rather than treatment as usual. This will allow us to ascertain whether there are any particular benefits to CBT or whether just having the opportunity to talk to a supportive, empathetic therapist can make a difference to adjustment outcomes. In line with suggestions for research in this area, general nurses will be trained and supervised to deliver the interventions [15].

### Aims

#### Primary Aim

1) To determine whether patients with early stage MS who undertake an 8 session CBT programme for adjustment to MS will demonstrate better adjustment (defined as psychological well-being and social and role adjustment) than those undergoing 8 sessions of Supportive Listening (SL).

#### Secondary Aims

2) To examine whether the CBT and SL groups differ on a range of secondary outcomes including quality of life, acceptance of illness and dysfunctional cognitions.

3) To examine whether changes in predefined psychological mechanisms act as mediators through which change/adjustment in our primary outcomes occurs. These proposed mediating factors are dysfunctional or unhelpful cognitions and behaviours, and acceptance of illness.

4) To examine whether patients' responses to treatment is moderated by therapeutic alliance factors, patients' treatment preference, engagement in homework tasks, and perceived social support.

5) To examine the cost-effectiveness of both interventions by taking into account benefits to patients, effects on health service usage and other costs to society, and cost of providing the interventions.

6) To evaluate both interventions from the perspective of the person with MS using in-depth interviews and qualitative analysis methods to elicit their experiences of the therapy, any changes it brought, and any helpful and unhelpful aspects.

## Methods/Design

### Design

The trial is a two arm randomized multi-centre parallel group controlled trial. Consenting participants who meet eligibility criteria are randomly allocated to receive either CBT for adjustment to MS or Supportive Listening (SL). The SL arm of the trial has been chosen over standard medical care as a comparison condition as it is an acceptable and plausible approach that will control for non-specific treatment factors such as support, therapist time and attention, and patient expectations of improvement. The full trial design is summarized in Figure 1.

**Figure 1 F1:**
[figure not shown]
**CONSORT flowchart of trial design**.

### Setting

The trial has two centers (Southampton and South London) and each center has one therapist who delivers both CBT and SL.

### Ethical approval

This study has been reviewed and approved by the Thames Valley Multi-centre Research Ethics Committee (ref: 07/MRE12/6)

### Participants

#### Sample size calculation

Since there were no available MS CBT trials using either of our primary outcomes we computed a power analysis calculation based on a recent CBT trial for depression in people with MS, which used the Beck Depression Inventory (BDI) as the primary outcome [28]. The BDI, like the GHQ (one of our primary outcomes) is a measure of affective distress. Using a conservative estimate for the within-group standard deviation the effect size from this study was .60. To achieve 80% power at alpha = 0.025 significance level (to adjust for two primary outcomes) we would need 55 patients in each group to detect an effect of this magnitude by an independent samples t-test. To allow for attrition of around 10% at follow-up we need to initially include 61 participants in each group. In our CBT for MS fatigue trial we only lost 3/72 patients to follow-up (4%).

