### Eligibility criteria

#### Inclusion criteria

Participants do not need to be currently experiencing distress, depression or any particular coping difficulties to be included in the study. However, they must:

- have a definite diagnosis of MS, of any type, confirmed by a neurologist.

- be diagnosed with MS within the last 10 years.

- have some degree of ambulation (with assistance if needed), equivalent to an Expanded Disability Status Scale (EDSS) score [32] of 6.5 or less.

- be stabilised on disease modifying or anti-depressant medication (if taking). For disease modifying drugs (e.g. interferon) patients must have been on medication for a minimum of 3 months. For anti-depressants, patients must be on a stable dose for a minimum of 2 months.

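### Splitting alpha as a fixed 0.025 per primary outcome is valid, but Holm's procedure gives more power at the same 5% family-wise error with no extra patients

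*Protocol article*

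**What the plan says.** The Abstract (Methods/Design) and the section Primary outcome measures name two primary outcomes, the GHQ and the WSAS, assessed at 12 months. The Primary Aim is stated as "better adjustment (defined as psychological well-being and social and role adjustment").

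The Sample size calculation takes one effect size from a depression trial that used the BDI: "Using a conservative estimate for the within-group standard deviation the effect size from this study was .60". It then says "To achieve 80% power at alpha = 0.025 significance level (to adjust for two primary outcomes"), and "we would need 55 patients in each group to detect an effect of this magnitude by an independent samples t-test". Attrition is added: "To allow for attrition of around 10% at follow-up we need to initially include 61 participants in each group".

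The section Statistical analysis plan specifies a linear mixed model with the baseline value of the outcome as a covariate. It gives no rule for testing the two outcomes together. The 0.025 in the sample size section is thus the only multiplicity rule in the document.

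**The concern.** If 0.025 is applied to each outcome whatever the other shows, the second outcome is held to a stricter threshold than a 5% family-wise error requires. Once one of the two null hypotheses has been rejected at 0.025, the other can be tested at 0.05 without inflating the error. A plan that omits this step loses power for nothing.

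The Primary Aim joins two components, while the 80% belongs to one test. The protocol does not say whether success means either outcome or both, and the most efficient testing rule depends on that answer.

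**Working it through.** **Inputs from the protocol.** Standardised effect d = 0.60, alpha 0.025 per outcome, 55 per group, independent samples t-test (df = 2 × 55 − 2 = 108).

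**Assumptions not in the protocol.** d = 0.60 on the WSAS as well as the GHQ (the protocol says "Since there were no available MS CBT trials using either of our primary outcomes"); a GHQ–WSAS correlation of 0.3 to 0.7; and, for the adjusted figures, a baseline-to-follow-up correlation of 0.5.

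**Step 1: reproduce the stated figure.** Noncentrality = d × √(n/2) = 0.60 × √27.5 = 3.146. The two-sided critical value at 0.025 is 2.273. Noncentral t gives power 80.7% at n = 55 and 79.9% at n = 54, so 55 is right and the alpha is two-sided. For attrition, 61 × 0.9 = 54.9, or about 55.

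**Step 2: family-wise error under Holm.** If both nulls are true, a false rejection needs the smaller p-value to be at most 0.025, with probability at most 2 × 0.025 = 0.05. If one null is true, a false rejection needs that outcome's p-value to be at most 0.05. The error is at most 5% in either case, as with the fixed split.

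**Step 3: power with the unadjusted t-test.** The two t statistics each have noncentrality 3.146, and the correlation is as assumed. The critical value at 0.05 is 1.982.
- Both at fixed 0.025: both statistics exceed 2.273.
- Both under Holm: both exceed 1.982 and the larger exceeds 2.273.
- Both at 0.05: both exceed 1.982.

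Simulation of correlated t statistics, d = 0.60 on both:

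| Correlation | Both, fixed 0.025 | Both, Holm | Both, 0.05 each | At least one at 0.025 |
|---|---|---|---|---|
| 0.3 | 68% | 78% | 78% | 94% |
| 0.5 | 70% | 79% | 80% | 92% |
| 0.7 | 72% | 80% | 81% | 89% |

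The power for a single named outcome also rises under Holm, from 80.7% to about 85–86% over the same correlations. The chance of at least one success is the same under both procedures, because Holm's first step is the Bonferroni test.

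**Step 4: allow for the planned baseline adjustment.** A baseline correlation of 0.5 multiplies the residual variance by 1 − 0.5² = 0.75. The effective effect is 0.60/√0.75 = 0.693 and the noncentrality is 0.693 × √27.5 = 3.63. With residual correlations of 0.3 to 0.7 between the outcomes, both are significant with probability about 84–86% at fixed 0.025 and 90–91% under Holm. This treats the 12-month comparison as a covariance analysis; the full mixed model was not simulated.

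**Step 5: unequal effects.** With d = 0.60 and 0.40, correlation 0.5 and no adjustment, the figures are about 40% (fixed 0.025) and 51% (Holm).

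**The case against.** The strongest reply is that nothing in the Sample size calculation is wrong. It sizes one test and says why alpha is 0.025. A reader might infer from the wording of the Primary Aim that 80% is claimed for both outcomes jointly and that the trial is therefore too small. The documents do not support this. No section promises joint power or says both outcomes must succeed, and the Primary Aim's parenthesis defines a construct rather than a success rule. This part of the reply stands.

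Second, the argument can look inconsistent. If both outcomes are required, no split is needed, and 0.05 each does slightly better than Holm (79.7% against 78.9% at correlation 0.5). If either may be claimed, joint power is not the main figure. The premise is right, but it does not rescue the fixed split. Under the first reading the split is unnecessary, and under the second Holm still raises the power of each outcome.

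Third, the figure of about 70% belongs to an unadjusted t-test, whereas the planned model adjusts for baseline. This stands: at a baseline correlation of 0.5 joint power is above 80% even at fixed 0.025, and Holm's gain falls from about 9 points to about 6.

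Fourth, 0.025 may be only a planning value, with the testing rule left to a separate analysis plan. That is possible. It is still the only rule stated here, and Holm is compatible with the same planning alpha.

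A reader might also infer that 0.60 is untenable because it comes from a depression trial, whereas here "Participants do not need to be currently experiencing distress, depression or any particular coping difficulties to be included in the study". The protocol discloses the source and describes its standard deviation as conservative. It gives no figure from which a smaller effect could be derived, so the documents do not show that the power is overstated.

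**Conclusion.** The point holds as an efficiency improvement. Fixed 0.025 per outcome is valid, the 55 per group reproduces, and no power claim in the protocol is false. Holm gives the same family-wise protection and is never less powerful.

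Under the assumptions listed, it adds roughly 8 to 10 percentage points to the chance of showing both effects with the unadjusted test, and about 5 to 6 points with baseline adjustment. These sizes are conditional. They depend mildly on the correlation between the outcomes and strongly on the WSAS effect, for which the protocol gives no value. Neither 70% nor 79% should be quoted without those conditions.

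**What to change.** 1. In the section Statistical analysis plan, state that the smaller of the two 12-month p-values (GHQ, WSAS) is tested at 0.025 and, only if it is significant, the other is tested at 0.05.
2. If success is meant to require both outcomes, say so and test each at 0.05 instead. No alpha split is needed in that case.
3. In the Sample size calculation, label the 80% as power per outcome at d = 0.60. A both-outcome figure could be added, with its assumed effects and correlation. A line for smaller effects would be optional disclosure and would not change the design.

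The cost is two or three sentences. Holm's first step is still 0.025, so 55 analysed and 61 randomised per arm stand. The one practical consequence is in reporting: 97.5% confidence intervals match the fixed split exactly but not the second Holm step, so the interval level to be reported should be stated along with the rule.

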### Eligibility criteria

#### Inclusion criteria

Participants do not need to be currently experiencing distress, depression or any particular coping difficulties to be included in the study. However, they must:

- have a definite diagnosis of MS, of any type, confirmed by a neurologist.

- be diagnosed with MS within the last 10 years.

- have some degree of ambulation (with assistance if needed), equivalent to an Expanded Disability Status Scale (EDSS) score [32] of 6.5 or less.

- be stabilised on disease modifying or anti-depressant medication (if taking). For disease modifying drugs (e.g. interferon) patients must have been on medication for a minimum of 3 months. For anti-depressants, patients must be on a stable dose for a minimum of 2 months.

#### Exclusion criteria

Patients will be excluded from the study if they:

- have gross cognitive impairment that would make participation in 8 one hour sessions of talking therapy problematic or distressing. This will be assessed using the Telephone Interview for Cognitive Status-Modified; TICS-M [33] administered by the trial co-ordinator during screening. Patients with a score of less than 20 will be excluded.

- have serious psychological disorders for which treatment would be inappropriate (including psychotic disorders or active substance abuse problems).

- have other co-morbid serious chronic illnesses (e.g. a malignancy).

- are currently participating in other psychological therapies or have participated in other therapies within the last 2 months.

- are considered by their treating physician to have needs that are more appropriately addressed by a referral to another psychological service (e.g. psychiatrist, clinical psychologist, MS special mental health nurse).

#### Source of participants

Participants will be recruited from two National Health Service (NHS) MS centers in the Southampton area (Southampton University Hospital Trust; SUHT) and South London (King's College Hospital Trust; KCHT).

#### Recruitment and consent process

Patients seen or in contact with these services during the trial period will be informed about the trial if they appear to meet eligibility criteria. During routine consultations, either one of the MS nurses or one of the neurologists will use an eligibility checklist, detailing the key inclusion and exclusion criteria, to identify suitable patients. The nurse/neurologist will hand over a Participant Information Sheet with a contact details reply slip, consent form, and freepost envelope to all that are potentially eligible and interested. If the participant is keen to be involved the nurse/neurologist will ask permission to write down the participant's contact details and freepost it back to the trial co-ordinator so that she can contact them about the project. Alternatively the patient can choose to initiate contact with the research team by posting the contact details form back to the trial co-ordinator, or getting in touch by telephone or email.

Once contact is made with the trial co-ordinator the patient's questions will be answered and their understanding of what is involved in the trial verified. Consent forms will be returned to the trial co-ordinator by freepost for those who wish to take part. On the form, participants are given the choice to consent to the therapy trial and questionnaire assessments only, or to an additional in-depth telephone interview after their therapy programme has been completed.

